### Documentation of adverse events

For the immunogenicity study, any AE occurring within 3 weeks (minimum 17 days) following vaccination will be recorded on the AE Page of the CRF, irrespective of its severity or potential relationship to the vaccine.

Any SAE brought to the attention of the investigator from study start up to 6 months (at least 180 days) after vaccination of that subject will be recorded. AEs not previously documented in the adverse event form will be recorded in the AE page of the CRF. AEs should be documented in terms of signs and symptoms observed by the investigator or reported by subjects. Whenever possible, a medical diagnosis should be made. The nature of each event, date and (where appropriate) time of onset, outcome, severity and causal relationship should be established. Details of any symptomatic/corrective treatment should be recorded on the appropriate page of the CRF.

Hospitalisation for routine clinical procedures (including hospitalisation for "social" reasons) that are not the result of an AE are not considered AEs but will be recorded on the AE page of the CRF. The same applies for hospitalisation for elective procedures related to a pre-existing condition that did not increase in severity or frequency during the study. If hospitalisation was planned before first administration of the vaccine, it will be documented in the Medical History Page of the CRF (see below).

The following events will be documented in the Medical History Page of the CRF:

- AEs which occur after informed consent was obtained, but before the first vaccine administration
- Pre-existing conditions or signs and/or symptoms present in a subject before study start. This includes conditions which were not recognized at study entry but later during the study period
- Hospitalisation arising from a pre-existing condition and planned before the first administration of the vaccine

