- Trial blood and Orasure samples will be collected to measure the antibody, T- and B-cellular and local antibody responses respectively.
- Schedule the next clinic visit.

Fourth visit: Day 21 ( $\pm 4$  days)

During this visit the following will be carried out and recorded in the CRF;

- Collect and discuss Adverse Event Form.
- Obtain interim history, including post injection reactions, adverse events and use of prescription and relief medication
- Trial blood samples will be collected by venepuncture.

Fifth visit: 3 months ( $\pm 31$  days) post 2nd vaccination

- Subjects will be asked to give a trial blood sample.
- An Orasure sample will be collected.

Sixth visit: 6 months ( $\pm 31$  days) post 2nd vaccination

- Subjects will be asked to give a trial blood sample.
- An Orasure sample will be collected.

Seventh visit: 9 months ( $\pm 31$  days) post 2nd vaccination

- Subjects will be asked to give a trial blood sample.
- An Orasure sample will be collected.

Eighth visit: 12 months ( $\pm 31$  days) post 2nd vaccination

- Subjects will be asked to give a trial blood samples.
- Orasure samples will be collected.

Ninth visit: 18 months ( $\pm 31$  days) post 2nd vaccination

- Subjects will be asked to give a trial blood samples.
- Orasure samples will be collected.

Eleventh visit: 12 months ( $\pm 31$  days) post 2nd vaccination

- Subjects will be asked to give a trial blood samples.
- Orasure samples will be collected.

Laboratory Analysis for the immunogenicity study

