#### Documentation of solicited adverse events

Solicited AEs are precisely defined events that the subjects are specifically asked about and which are documented by the subjects in the adverse event form. This form will be the source document.

The following local AEs at the vaccine injection site (injections site reactions) will be documented in the Adverse Event Form:

- Pain
- Erythema
- Ecchymosis
- Induration
- Itching
- Swelling

---

 A procedure which may take place during the study period and should not interfere with the vaccine administration or any of the ongoing protocol-specific procedures.

The following solicited systemic AEs will be documented in the adverse event form and transcribed by the investigator into the CRF:

- Body temperature (oral)  $\geq 38^{\circ}\text{C}$
- Malaise
- Shivering
- Fatigue
- Headache
- Sweating
- Myalgia
- Arthralgia
- Diarrhoea
- Respiratory symptoms

An Adverse Event Form will be issued to all subjects instructing them to record their daily local and systemic adverse events for as long as symptoms persist. The subjects will provide information on the presence or absence of solicited local and systemic adverse events. The use of antipyretic/relief medication and any changes in medication will also be recorded. Subjects will score the severity of symptoms as follows:

Blank – no adverse symptoms

1 -symptom occurred but not severe enough to cause inconvenience

2 -symptom occurred severe enough to interfere with daily activities but required minimal or no medical intervention

3-symptom occurred severe enough to markedly interfere with daily activities; required medical consultation

At each visit for the immunogenicity study, all AEs, either observed by the clinical investigator or his nominee or reported by the subjects spontaneously or in response to a direct question will be evaluated by the investigator.

As a consistent method to find out about adverse events, the investigator should use a non-leading question, such as:

"Have you felt different since receiving the vaccine or since the previous visit?"

The subjects will be instructed to contact the clinical investigators immediately should they experience any signs or symptoms they perceive as serious during the period extending from the first study-specific procedure up to and including 6 months (minimum 180 days) after the last administration of the vaccine.

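### For the immunogenicity cohort, the protocol contradicts itself on whether subjects are asked about adverse events after Day 21, although serious events are to be recorded to at least Day 180

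*Protocol*

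**What the plan says.** Four places in the protocol bear on this.

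- **Section 9, Documentation of adverse events.** In the immunogenicity cohort the general rule is that "any AE occurring within 3 weeks (minimum 17 days) following vaccination will be recorded on the AE Page of the CRF". For serious events the period is longer: "Any SAE brought to the attention of the investigator from study start up to 6 months (at least 180 days) after vaccination" is to be recorded.
- **Section 9, Documentation of solicited adverse events.** The investigator is to evaluate adverse events at every visit: "At each visit for the immunogenicity study, all AEs, either observed by the clinical investigator or his nominee or reported by the subjects spontaneously". Answers to a direct question count as well. A sample question is supplied: "Have you felt different since receiving the vaccine or since the previous visit". Subjects are also told to contact the investigators about anything they perceive as serious, for at least 180 days.
- **Section 5, study procedure for the immunogenicity and kinetic studies.** The adverse event form is handed out on Day 0 and reviewed on Days 7 and 14. At Day 21 the step is "Collect and discuss Adverse Event Form", together with an interim history. At the 3-, 6- and 9-month visits the whole list is "Subjects will be asked to give a trial blood sample" and an oral fluid sample. The 6-month visit has a window of ±31 days. These visits are counted from a second vaccination.
- **Table 5.1.** The adverse-event row is ticked on Days 0, 7 and 14 and in the next two columns, labelled 3 and 9 months. It is blank under 6 months.

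The design statement in Section 5 and the treatment description in Section 7 give one dose.

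**The concern.** The recording window for serious events is about 180 days, but the lists that site staff work from mention adverse events only up to Day 21. A nurse who follows the 3- or 6-month list takes two samples and asks nothing. The 6-month visit can also take place before the 180-day minimum is reached, so even a question asked then may not cover the whole window.

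Adverse events in all volunteers are the primary endpoint, and Section 9 defines serious events as a subset of them. Section 13 justifies the study partly by reactions that may occur very rarely. If subjects are questioned up to Day 21 and only volunteer events afterwards, any serious-event count over the window would favour early onset because of how it was collected. The subjects are already seen in person at 3 and 6 months, so the gap is avoidable.

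**Working it through.** **Inputs, all from the protocol**

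- Serious-event window: at least 180 days (Section 9).
- Recording of all adverse events: 3 weeks, minimum 17 days (Section 9).
- Last visit whose procedure list names adverse events: Day 21 ± 4 (Section 5).
- Long-term visits: 3, 6 and 9 months, each ± 31 days (Section 5).
- Assumption: a month is 30 to 30.5 days, and visits are counted from the single vaccination.

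**The plan's own figures**

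- 6 × 30 = 180 days, the stated minimum for serious events.
- 21 − 4 = 17 days, the stated minimum for all adverse events. It equals the earliest permitted Day 21 visit.
- The same calculation for the 6-month visit gives 180 − 31 = 149, not 180. The 180-day minimum is therefore not secured by a visit window in the way the 17-day minimum is.

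**Reading A: the Section 5 visit lists govern**

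- Days after the last listed enquiry: 180 − 21 = 159.
- Share of the window: 159/180 = 88.3%.
- With the Day 21 visit at Day 25 or Day 17: 155/180 = 86.1% to 163/180 = 90.6%.

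**Reading B: the each-visit rule in Section 9 governs**

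- Earliest 6-month visit: 180 − 31 = Day 149, or 183 − 31 = Day 152.
- Days from that visit to Day 180: 180 − 149 = 31 (17.2%), or 180 − 152 = 28 (15.6%).
- If the visit takes place at Day 180 or later, nothing is left open.
- The 9-month visit (earliest 270 − 31 = Day 239) would ask about the time since the previous visit, so it would reach back over the remaining days.

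**Reading C: only the 3-month tick in Table 5.1 counts within the window**

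- With a 30-day month, the 3-month visit falls between Day 90 − 31 = 59 and Day 90 + 31 = 121.
- Share after it: (180 − 59)/180 = 67.2% down to (180 − 121)/180 = 32.8%. With a 30.5-day month the lower figure is (180 − 122.5)/180 = 31.9%.

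**Side by side**

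| Governing text | Share of the 180 days after the last in-window enquiry |
|---|---|
| Section 5 visit lists | 88% (86% to 91%) |
| Table 5.1, 3-month tick only | 32% to 67% |
| Section 9, each visit | 0% to 17% |

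**Reference point.** If the long-term visits were counted from a dose three weeks later while the safety window ran from the first, the earliest 6-month visit would be Day 149 + 21 = 170 to Day 152 + 21 = 173. That is still 7 to 10 days short of Day 180. The documents do not settle which reference point is meant.

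**The case against.** The strongest reply is that Section 9 already requires what is asked for. Its each-visit rule has no Day 21 cut-off, it scripts a question reaching back to the previous visit, and the 3-, 6- and 9-month visits are immunogenicity visits. The Section 5 lists are silent on adverse events at those visits; they do not exclude them. Table 5.1 also ticks adverse-event collection beyond Day 14. A reader might infer from the visit lists that all questioning stops at Day 21 and that ascertainment is passive for 88% of the window. The documents do not support that as a flat statement, and it holds only if the lists are taken as the complete instruction.

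Other parts of the reply also have force.

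- No text ties the end of serious-event capture to the 6-month visit.
- Subjects are told to report serious symptoms for at least 180 days. The investigators may consult hospital records (Section 11), and subjects come mainly from the hospital's and university's own employees and students (Section 2). Capture after Day 21 would be weaker under the visit lists, but not absent.
- The protocol plans no 6-month serious-event rate. The point concerns the subset of up to 500 to 550 subjects, not all of the up to 8000 who return forms.

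The contradiction itself is not answered. The each-visit rule stands under the heading for solicited events, and its question is given as an example of what the investigator should ask. The 3-week limit on recording all adverse events fits the visit lists stopping at Day 21, so staff could reasonably take the lists as complete. Table 5.1 does not decide the matter: it has no Day 21 column, and its column order (3, 9, 6 months) may come from the PDF reading, so it carries no weight alone.

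**Conclusion.** The point holds as an internal contradiction. The Section 5 procedure lists, the each-visit rule in Section 9 and Table 5.1 disagree on whether and when the immunogenicity cohort is asked about adverse events after Day 21.

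The part of the 180-day window after the last in-window enquiry is up to 159 days (88%) if the visit lists govern, and at most about 28 to 31 days (16% to 17%) if Section 9 governs. The second figure comes from the ±31-day window of the 6-month visit. It rests on 30 to 30.5 days per month and on counting from the single vaccination.

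A reader might go further and put a percentage on serious events missed. The documents give no reporting fraction for volunteered events, so no such figure can be supported. The matter is worth correcting because it concerns safety data collection, which an analysis plan cannot repair afterwards.

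**What to change.** 1. In Section 5, add the Section 9 non-leading question and an explicit serious-event check to the 3- and 6-month visit lists, and mark Table 5.1 to match.
2. State that where the 6-month visit falls before Day 180, the remaining days to Day 180 are asked about at the next visit.
3. Reconcile the reference point of the long-term visits, now a second vaccination, with the one-dose descriptions in Sections 5 and 7, so that the visit window and the 180-day window have an unambiguous common start.

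This is a wording change plus one extra question at visits that already take place. The drawback is some recall error for subjects whose remaining days are covered only at 9 months, at least 239 − 180 = 59 days after the window closes. Whether to report serious events separately for the periods before and after Day 21 can be left to the analysis plan.

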### Reporting of serious adverse events

All SAEs will be reported immediately by the investigator without filtration into SYSVAK according to national guidelines, independent of their association or causal relation to the vaccine. The initial notification should include all known information regarding the SAE (which may be

minimal, but should include sufficient information to permit identification of the reporter, the subject, the vaccine the SAE, and the date of onset of the SAE). The initial report should then be followed by submission of a completed SAE report to SYSVAK as soon as possible but at latest within the time frame specified in the national guidelines.

The completed SAE Report Form should detail all relevant aspects of the SAE, all actions taken by the investigator, the causality, and the outcome of the event. Any new information obtained regarding the SAE must be reported immediately. The SAE Report Forms should be used for documentation of the SAE, any actions taken, the outcome, and for follow-up reports. When applicable, hospital case records and autopsy reports should be obtained by the investigator and forwarded to the Study Contact for SAE Reporting.

The investigator must report SAEs to the appropriate Ethics Committee, if requested by the committee, and/or according to local legal requirements.

The reporting obligations for SUSARs will be fulfilled as required by the applicable law.

#### Causality of adverse events

Every effort should be made by the investigator to explain any AE and assess its potential causal relationship to administration of the vaccine. This applies to all AEs, i.e. to both non-serious and serious adverse events.

To which degree of certainty an AE can be attributed to administration of the vaccine or to alternative causes (e.g. natural history of the underlying diseases, concomitant therapy) will be determined by how well the event can be understood in terms of one or more of the following:

- A reaction of a similar nature has been previously observed with this type of medicinal product and/or formulation
- The event has often been reported in literature for similar types of medicinal products
- The event has been temporally associated with vaccine administration or reproduced on re-administration of the vaccine

By definition, all solicited local AEs occurring at the application site (i.e. all solicited local reactions) will be considered related to the vaccine administration (injection site reactions).

Causality of all other AEs should be assessed by the investigator based on the following:

In your opinion, is there a reasonable possibility that the AE was caused by the vaccine?

- |           |                                                                                                                                                                                                  |
|-----------|--------------------------------------------------------------------------------------------------------------------------------------------------------------------------------------------------|
| Related   | there is suspicion that there is a relationship between vaccine and AE (without determining the extent of probability); there is a reasonable possibility that the vaccine contributed to the AE |
| Unrelated | there is no suspicion that there is a relationship between vaccine and AE; there are other more likely causes and administration of the vaccine is not suspected to have contributed to the AE   |

### Severity of adverse events

The severity of unsolicited AEs will be graded on a 3-point scale as follows:

| Grade        | Definition                                                                                                                                                                               |
|--------------|------------------------------------------------------------------------------------------------------------------------------------------------------------------------------------------|
| 1 (mild)     | Discomfort noted, but no disruption of normal daily activity; slightly bothersome; relieved with or without symptomatic treatment.                                                       |
| 2 (moderate) | Discomfort sufficient to reduce or affect normal daily activity to some degree; bothersome; interferes with normal daily activities; only partially relieved with symptomatic treatment. |
| 3 (severe)   | Discomfort sufficient to reduce or affect normal daily activity considerably; prevents regular activities; not relieved with symptomatic treatment.                                      |

### Follow-up of ongoing adverse events and assessment of outcome

Follow-up of non-serious adverse events for subjects in the immunogenicity study.

Non-serious AEs already documented in the CRF at a previous assessment and designated as ‘ongoing’ should be reviewed at subsequent visits. If the event has resolved, the documentation in the CRF should be completed. If the frequency or severity of a non-serious AE changes significantly, a new record of the AE has to be started. If the AE becomes serious, the procedures for reporting of SAEs have to be followed (see above).

Ongoing non-serious AEs will be followed until the end of the active study phase.

Outcome will be assessed as:

- 1 Resolved (no sequelae)
- 2 Resolved (with sequelae)
- 3 Ongoing
- 4 Death
- 5 Unknown

#### Follow-up of serious adverse events

All SAEs must be followed-up according to national guidelines until the event has either resolved, subsided, stabilized, disappeared, or is otherwise explained, or the study subject is lost to follow-up, but no longer than 6 months after the last vaccination.

All follow-up activities must be reported in a timely manner to SYSVAK. All fields of the form with additional or changed information must be completed and the SAE Report Form should be forwarded to the Study Contact for SAE Reporting as soon as possible but at the latest within 7 calendar days after receipt of the new information. Reports related to the subsequent course of any SAE reported for any subject will be submitted according to National guidelines.

#### Treatment of adverse events

Treatment of any AE is at the sole discretion of the investigator and according to current available best treatment. The applied measures should be recorded in the CRF.

## **10. Statistics**

### **1. A description of the statistical methods to be employed**

The main aim of this study is to evaluate the tolerability and immunogenicity of the pandemic H1N1 vaccine. Adverse reactions will be collected from up to 8000 volunteers and will be analysed by the Fisher's exact and Mantel-Haenszel tests. In the immunogenicity study, immunological analyses will be available from up to 550 volunteers. The number of responders with detectable antibody was compared by the Mantel-Haenszel test using the Breslow-Day test

analysis for the homogeneity of the odd ratios. The paired two-sided Student's t-test will be used to analyse the antibody and cellular responses.

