## **4. TRIAL OBJECTIVES AND PURPOSE**

The objectives and purpose of this trial are:

- 1) Evaluation of the local and systemic safety and tolerability of parenterally administered adjuvanted H1N1 influenza vaccine in all recipients of vaccine at Haukeland University Hospital.

To evaluate the immunogenicity of a pandemic H1N1 influenza vaccine including:

- 2) Provide a detailed time course of the immune response to vaccination with a novel influenza H1N1 virus including the kinetics of the T-cell, B-cell and antibody responses in up to 60 volunteers
- 3) Investigate the long-lasting immunity induced by the vaccine
- 4) Examine the ability of the vaccine to induce cross-reactive immunity to H1N1 strains
- 5) Evaluate the quality of the immune response induced by the vaccine.
- 6) Examine the immune response after seasonal influenza vaccination in this study population

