## **5 TRIAL DESIGN**

### **1. A specific statement of the primary endpoints and secondary endpoints to be measured by the trial**

The primary endpoints of the trial are the local and systemic adverse events and tolerability of parenterally administered adjuvanted H1N1 influenza vaccine in all volunteers. The secondary

endpoints are the evaluation of the immunogenicity of adjuvanted H1N1 influenza vaccine and the ability of the vaccine to meet the CHMP evaluation criteria in a subset of volunteers.

The immunogenicity of the H1N1 vaccine will be assessed through the induction of specific local and systemic antibody and cellular immune responses, and analyses of the epitopes to which the response is directed. Furthermore, the capacity of the vaccine to elicit cross reactive and long lasting immunity will be evaluated. In a pandemic situation, an important aspect is the rapidity of the immune response to the H1N1 vaccine and therefore the detailed kinetics of the immune response will be investigated.

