#### A description of the type/design of trial to be conducted

The clinical trial will be an open study, all subjects eligible for pandemic vaccination at Haukeland University Hospital will receive one dose of vaccine by intramuscular injection into the deltoid muscle. An adverse events form will be dispensed to all subjects.

In the immunogenicity study, blood and oral fluid samples will be collected at the appropriate days (e.g. 0, 7, 14 and 21) after pH1N1 and seasonal vaccination. This study is an open study and all subjects will receive the Pandemrix vaccine, however, the trial samples will be coded with a unique number. Serological assays will be conducted at The University of Bergen and also blinded by the reference laboratories, National Institute for Biological Standards and Control (NIBSC), Health Protection Agency (HPA) and University of Siena (UNISI). Blood samples will also be collected at 3, 6, 9, 12, 18 and 24 months after pH1N1 and seasonal vaccination. The kinetics of the immune response will be studied at the University of Bergen.

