## 9 Assessment of Safety

One of the main aims of this study is to evaluate the occurrence of adverse events in people vaccinated with the pandemic A/H1N1 vaccine. All subjects will be asked to fill in the adverse events form to record the incidence of local and systemic solicited side reactions. All adverse events and their follow up will be recorded in SYSVAK according to the national guidelines.

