## **13. Ethics**

The pandemic A/H1N1 vaccine will be used to provide protection against pandemic influenza in millions of people. As front line health care workers are a prioritized group it is important to compile a large database to assess the incidence of adverse reactions. The current safety database for the mock up vaccine has been considered sufficient by the CHMP to describe adverse reactions that occur uncommonly and to give an indication of any rare events. However, some adverse reactions may occur very rarely after influenza vaccination. We cannot predict if higher rates might be observed with Pandemrix for pandemic H1N1 virus compared to seasonal influenza vaccines, but it is vitally important to have data available from a large cohort of vaccinees.

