## **16 Publication Policy**

The results of this study will be published in international peer reviewed journals. A substantial amount of information will be generated by the study. Publications arising out of the work will focus on:

- The safety and comparative reactogenicity of pandemic H1N1 vaccines in an immunologically naïve population.
- The kinetics of the antibody and B and T cellular responses
- Evaluation of the ability of adjuvanted pandemic H1N1 influenza vaccine to fulfil the CHMP criteria
- Detailed time course of the immune response to vaccination with a novel H1N1 influenza subtype including the kinetics and quality of the serum antibody and T and B cellular responses and epitope mapping
- The longevity of the immunity induced by the vaccine
- The ability of the vaccine to elicit cross reactive immunity against other H1 strains.

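### The only analysis stated for the primary safety endpoint is a pair of between-group tests with no groups named, in a one-arm study whose aim is the incidence of reactions

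*Protocol*

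**What the plan says.** Section 5.1 sets the primary endpoint: "The primary endpoints of the trial are the local and systemic adverse events and tolerability", in all volunteers. The first objective in section 4 matches it: "Evaluation of the local and systemic safety and tolerability of parenterally administered adjuvanted H1N1 influenza vaccine in all recipients of vaccine".

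The design has one arm. Section 5 states "The clinical trial will be an open study, all subjects eligible for pandemic vaccination at Haukeland University Hospital will receive one dose of vaccine" and, further on, "This study is an open study and all subjects will receive the Pandemrix vaccine". Section 7.1 repeats the single dose, and the opening note of section 9a restricts the word vaccine to the pandemic product.

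The protocol states the purpose of the safety data twice. In section 9: "All subjects will be asked to fill in the adverse events form to record the incidence of local and systemic solicited side reactions". In section 13: "it is important to compile a large database to assess the incidence of adverse reactions".

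The analysis is in section 10.1: "Adverse reactions will be collected from up to 8000 volunteers and will be analysed by the Fisher's exact and Mantel-Haenszel tests". No grouping factor, stratifying variable, reference rate or estimated quantity goes with it. Section 10.2 adds only that there will be at most 8000 reports. Section 16 lists as a publication topic "The safety and comparative reactogenicity of pandemic H1N1 vaccines", without a comparator.

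**The concern.** Fisher's exact test asks whether a proportion differs between groups. The Mantel-Haenszel test asks the same within strata. Neither returns the size of a proportion in a single cohort, which is what the first objective and sections 9 and 13 call for.

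The mismatch affects the only analysis that the protocol attaches to its primary endpoint. Someone following section 10.1 literally would have to choose a split of the cohort, possibly after seeing the data, and would report p-values for that split. The reaction rates, their precision and a bound for events not seen would have no stated place in the primary analysis. Section 13 justifies the large cohort partly because some reactions may be very rare, so that bound matters here.

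**Working it through.** **Is there a figure to reproduce?** No. The protocol gives no significance level, power, reference rate or margin for safety, and 8000 is a ceiling set by the number vaccinated.

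**What the stated tests can show.** Suppose 8000 subjects are divided 4000/4000 on some factor (an assumption, since none is named) and the reaction rate is the same in both halves.

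- 400/4000 v 400/4000 (10%): odds ratio 1, Fisher p = 1.0
- 2000/4000 v 2000/4000 (50%): odds ratio 1, p = 1.0
- 3600/4000 v 3600/4000 (90%): odds ratio 1, p = 1.0

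Three very different safety profiles give the same output, because the test responds to the difference between groups and not to the level.

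**What estimation would show.** For x events in n forms, the two-sided Clopper-Pearson 95% limits are

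- lower = 0.025 quantile of Beta(x, n − x + 1)
- upper = 0.975 quantile of Beta(x + 1, n − x)

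For x = 0, the two-sided upper limit is 1 − 0.025^(1/n) and the one-sided 95% bound is 1 − 0.05^(1/n).

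Only n = 8000 comes from the protocol (section 10.2, as a maximum). The reaction rates and the smaller n are assumptions that show the range.

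| Forms | 50% | 10% | 1% | 0.1% | Zero events: two-sided / one-sided |
|---|---|---|---|---|---|
| 8000 | 48.90–51.10% | 9.35–10.68% | 0.79–1.24% | 0.043–0.197% | 0.046% / 0.037% |
| 4000 | 48.44–51.56% | 9.09–10.97% | 0.72–1.36% | 0.027–0.256% | 0.092% / 0.075% |
| 1000 | 46.85–53.15% | 8.21–12.03% | 0.48–1.83% | 0.003–0.556% | 0.368% / 0.299% |

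The two zero-event figures answer slightly different questions, so the plan has to say which it uses.

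**Which denominator.** On the form a blank means no symptom (section 9, solicited events), so a returned blank form is a non-event and an unreturned form is missing. If, as an assumption, 4000 of 8000 forms came back and 400 reported a reaction, the rate is 400/4000 = 10% of forms but 400/8000 = 5% of those vaccinated. That gap of 5 points is far wider than the interval of about ±0.9 points at n = 4000.

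**Unsolicited events.** Section 9 (documentation of adverse events) records these on the case report form of the immunogenicity study. At the 500 subjects of section 10.2, zero events gives 1 − 0.025^(1/500) = 0.735% (two-sided) or 1 − 0.05^(1/500) = 0.597% (one-sided). Both are about 16 times the limits at 8000.

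**Which events.** Section 9 lists 6 local and 10 systemic solicited items, 16 in all, each scored blank or 1 to 3.

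**The case against.** The strongest reply is that counting events over forms needs no inferential test, that sections 9 and 13 already declare incidence as the aim, and that section 10.1 nowhere says the tests replace tabulation. Confidence intervals, summary tables and subgroup definitions commonly go into a statistical analysis plan, which may exist. Both tests are also valid in a one-arm cohort for contrasts between kinds of subject. No success criterion, margin or stopping threshold depends on their p-values.

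Most of this stands, and it limits the point. A reader might infer that the trial cannot produce reaction rates or meet its first objective. The documents do not support that, because the forms can be tabulated and tabulation is evidently intended. A reader might also call the tests invalid, but they only lack named groups.

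Two further inferences go too far. The first takes comparative reactogenicity in section 16 as a commitment to a comparison within the trial. It is a publication topic and may mean comparison with outside data. Nor does seasonal vaccination, which the immunogenicity cohort is followed after, supply a comparator, given the definition in section 9a. The second is a false-positive rate across the 16 items. That would need a significance level, a factor and independence between symptoms, none of which the protocol gives, and it would measure multiplicity, a different issue.

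The appeal to an unseen analysis plan does not remove the point. The protocol is not silent: it names specific methods for its primary endpoint, and they do not estimate the quantity it says it wants.

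**Conclusion.** The point holds, limited to the stated analysis. Section 10.1 assigns only between-group tests, without groups, to the primary endpoint of a one-arm, one-vaccine study that aims at incidence in all recipients. Those tests do not estimate incidence, although the forms can.

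The structural conclusion needs no numerical assumption. The gain from estimation is indicated by an exact 95% interval of 9.35 to 10.68% for an assumed 10% reaction at 8000 forms, and by the zero-event limits of 0.046% (two-sided) or 0.037% (one-sided). These rest on the protocol's maximum being reached and become wider with fewer forms. They describe sampling error only and do not cover selective return of forms.

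This should be fixed, but it does not undermine the trial: the data are unaffected and no decision rule depends on the p-values.

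**What to change.** Replace the adverse-reaction sentence in section 10.1 with text to this effect:

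- **Primary safety analysis.** The proportion of subjects with each of the 16 solicited events, any local event, any systemic event and any grade 3 event, overall and by grade, each with a two-sided Clopper-Pearson 95% confidence interval.
- **Denominator.** Forms returned, with the number vaccinated and the return rate reported alongside.
- **Unsolicited adverse events.** Reported separately, with the immunogenicity cohort as the denominator.
- **Zero events.** State whether the limit is the upper end of the two-sided 95% interval or the one-sided 95% bound.
- **Fisher's exact and Mantel-Haenszel tests.** Kept only as comparisons labelled exploratory, on factors named in advance and available for the subjects analysed. Influenza vaccination history is shown as recorded only at the first visit of the immunogenicity and kinetic studies. A comparison on it should therefore be limited to that cohort, unless the adverse event form also collects it.

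Section 16 can stay as it is, since changing a publication topic alters no result. The cost is a few sentences. The primary estimates need no new data beyond the forms and the vaccination count; a vaccination-history comparison in the whole cohort might.
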